**Figure 2. f2:**
[figure not shown]
Overview of participation timeline and study procedures.

**3.4.4.1
Baseline study visit
**

Participant enrolment and baseline clinical assessment will be conducted in an appointment lasting up to 1 hour. All participants will be invited to attend this appointment face-to-face at the Clinical Research Facility (CRF) (Royal Infirmary of Edinburgh). Participants will be given the option to complete the baseline assessment in-person (at the Clinical Research Facility, CRF, RIE) or online via Near Me.

During this appointment, eligibility criteria will be checked again and individuals will give written consent to participate in the study. Written consent will either be on paper (if the appointment is in-person), or electronically (if the appointment is online). A structured clinical assessment will record:

Details of demographics and lifestyle (educational attainment, employment status, socioeconomic status, smoking status (current smoker/non-smoker, ex-smoker, never smoked), substance use, and alcohol use assessed using the Alcohol Use Disorders Identification Test, AUDIT (Saunders
*et al*., 1993))Sleep quality assessed using the Pittsburgh Sleep Quality Index (PSQI) (
Buysse *et al*., 1989) (licence agreement in place 04/03/24)Chronotype assessed using the Munich Chronotype Questionnaire (MCTQ) (
Roenneberg *et al*., 2003) (copyright license obtained 08/12/23)Global assessment of function (GAF) assessed using the WHODAS 2.0 (
Measuring Health and Disability, 2010;
Ustün *et al*., 2010)Past psychiatric history (including age of onset, number and timing of episodes of depression, hypomania and mania, and a detailed assessment of past and current medication use, including the Retrospective Assessment of the Lithium Response Phenotype (Alda) Scale (
Grof *et al*., 2002).

**3.4.4.2
Part A: Overnight experimental assessments
**

Two weeks prior to attending for the overnight experimental assessments, participants will be sent an actigraphy wristband and sleep diary, along with clear instructions for use (the actigraph can be preset to start recording when convenient). Daily light exposure and sleep-wake cycles will be monitored in the home setting for 10 days using the diary and wristband, as well as a record of daily caffeine and alcohol use. Participants will be given advice on limiting alcohol use, and on maintaining a regular sleep schedule for the duration of their participation.

In the rare occasion of a last-minute Part A cancellation, the appointment slot will be offered to an enrolled Control participant. In this instance, the actigraphy and sleep diary data will not be collected prior to the Part A overnight visits for that individual, and can be collected at another time point during the individual’s participation. This data is not required to meet the primary study outcomes.

Part A overnight experimental assessments will be conducted between the months of September-April inclusive to avoid the effects of too much light at night during the summer months.

Study Day 1

On Day 1, participants will attend the Clinical Research Facility in Edinburgh from 1700h. On arrival, there will be a check that participants still satisfy the inclusion and exclusion criteria and measurements of blood pressure, heart rate, height and weight will be taken. Participants will then be cannulated for the blood sampling used for melatonin measurements. A 2ml sample of blood will also be taken from the ‘bipolar disorder on Lithium’ group to test for lithium levels. An 8ml sample of blood will be collected and stored long-term for use in future ethically approved studies, including WP1 of the HELIOS-BD programme (wherein our collaborators in Newcastle/Northumbria will conduct retinal organoid research that is part of a separate ethics approval and protocol).

Participants will be required to ingest an eCelsius Performance telemetric temperature pill (BodyCAP, France) to monitor their core body temperature (CBT) throughout the first study night. The temperature-sensing pill is the size of a capsule tablet, does not record any information other than body temperature, and remains intact and will pass within 24–48 hours in the participant’s stool.

Participants will be offered meals as appropriate to the time of day and unlimited decaffeinated liquids. Participants will not be allowed to snack during the hours of blood sampling (19:00-06:00). From arrival at the CRF until lights out, participants will be kept under dim light conditions (<5 lux) until 2200h. During dim-light exposure, participants will not be allowed to use light-emitting devices such as mobile phones, tablets or e-readers. At 2200h, all lights will be turned off and participants will be invited to sleep. Participants can rise and turn on the lights at any time of their choosing from 0600h onwards.

During night 1, CBT will be measured with an ingestible eCelsius telemetric temperature pill, to allow us to schedule the light pulse during the subsequent night in reference to the temperature nadir. If the telemetric pill data cannot be collected (e.g. due to contraindication or data loss) then CBT nadir will be estimated using 12-day sleep diary. Blood sampling from a venous catheter will be performed hourly at night for baseline measurement of melatonin levels (1900h – 0600h). If at any point overnight it is no longer possible to use the cannula to obtain venous blood samples, up to 4 venous blood samples can be obtained via venepuncture. Samples will be centrifuged and blood plasma will be deep frozen until melatonin radioimmunoassay analysis.

Participants will be allowed to leave the Clinical Research Facility the next morning (Study Day 2) before 0900h, returning at 1700hr. Their venous cannula will be removed prior to their departure.

Study Day 2

On Study Day 2, participants will return to the CRF from 1700hr and will be subject to the same conditions as Study Day 1 (meals provided, unlimited decaffeinated liquids, no snacking, bed times and light exposure). Participants will be cannulated on arrival for the blood sampling used for melatonin measurements. During night 2, participants will be free to sleep from 2200h as they wish and are able to, except for the period of nocturnal light exposure for melatonin suppression when they need to stay awake with their eyes open.

Approximately 120 minutes before the CBT nadir, bilateral ocular application of Minims Tropicamide 1.0% will be carried out by a member of the research team to dilate the participant’s pupils. 90 minutes before the estimated CBT nadir, a member of the research team will expose participants to a 30-minute light stimulus. The light exposure will be delivered within a box measuring 100 × 80 × 50 cm. The box is painted white on the inside and contains an LED bulb, covered by a white shade with an aperture in the base. The front side of the box is open. Participants will be requested to keep their hands and head inside the box for 30-minutes, with eyes open throughout.

If the CBT measure is deemed to be inaccurate or unreliable (for example, in the case of data transmitting failure of the device to the receiver) the habitual mid-point of the participant’s sleep will be used as an indicator of the CBT nadir.

Blood sampling will be performed hourly at night to cover a period before and after the light exposure, for measurement of melatonin levels (1900h – 0600h). For the 90 minutes surrounding the light stimulation protocol (30 minutes prior, 30 minutes during, and 30 minutes post), blood samples will be collected at 15-minute intervals. If at any point overnight it is no longer possible to use the cannula to obtain venous blood samples, up to 4 venous blood samples can be obtained via venepuncture. Samples will be centrifuged and blood plasma will be deep frozen until melatonin radioimmunoassay analysis.

If the participant cannot complete the light stimulation protocol at the scheduled time due to an unforeseen issue (e.g. side effects from eye drops), the light stimulation protocol can be attempted/re-attempted within 1 hour of the scheduled time, at the discretion of the research staff, without needing to re-administer eye-drops. If light exposure is commenced but it is not possible to complete the full 30 minutes of exposure, the rest of the protocol procedures (e.g. blood sampling) will still be completed as planned (if possible). Light exposure will not be reattempted once the participant has been exposed to light, even if this is for a short period.

Study Day 3

On Study Day 3, participants can rise and turn on the lights at any time of their choosing from 0600h onwards. Their venous cannula will be removed and participants will be allowed to leave the Clinical Research Facility and go home. Due to the pupil dilation and disrupted sleep period, participants will be advised not to drive on Study Day 3 if they feel their vision has not returned to normal and it is unsafe to drive. Taxi transport will be provided if participants are unable to take public transport home.

After these assessments, all participants will be clinically assessed on the phone or via video call within 3 days to ensure that they have not experienced significant manic or depressive symptoms.

**3.4.4.3
Part B: Retinal assessments
**

Experimental assessments will be conducted at the Colour and EEG laboratories (Dugald Stewart Building, University of Edinburgh). Testing will be completed in two sessions lasting approximately 2-3 hours each: one for colour psychophysics and pupillary responses; the other for visual evoked potentials. Participants will be assessed within a single day (with at least a 1 hour break in between, to avoid fatigue) or in 2 separate sessions, according to their preference. On arrival, there will be a check that participants still satisfy the inclusion and exclusion criteria.

Session 1 - Colour psychophysics and pupillary responses (Colour lab)

Participants will perform the following set of tasks:

1) Trivector test from the Cambridge Colour Test (Metropsis, Cambridge Research Systems, UK): circa 10 minutes (including instructions and some practice). The test measures three thresholds: along the 1) protan (Long-wavelength or L-cone), 2) deutan (Mid-wavelength or M-cone), and 3) tritan (Short-wavelength, or S-cone) axes. This test uses three interleaved adaptive psychophysical staircases to achieve a fast and precise measurement of cone function. It starts with a chromatic contrast at the extreme end of display gamut and subsequently modulates contrast along confusion lines that isolate L, M and S-cone function. Participants detect the orientation of a Landolt C type stimulus (up, down, left or right) embedded with a luminance-variegated background. Their responses control target chromatic contrast, so that the distance from neutral grey (i.e., background chromaticity) decreases for correct responses and increases for incorrect responses. This test has been used in a range of clinical populations (e.g., Parkinson’s disease, optic neuropathy, multiple sclerosis).

2) Contrast sensitivity functions (evaluated using Cambridge Research Systems, UK equipment) will provide a full characterisation of spatial vision driven by luminance and colour. In this test, gratings are displayed in the centre of the screen at 5 different spatial frequencies (range: 0.5 – 6 cycles per degree). Participants are asked to adjust the contrast of the stimulus until it is just barely visible. This should take 25 minutes in total, including instructions and some practice.

3) Suprathreshold just noticeable differences (JNDs) for luminance-defined, red-orange and blue will be measured using custom-made psychophysical procedures implemented on specialist colour vision equipment (CRS, UK). Participants will be presented with two stimuli, one on each side of the fixation cross. One of the two stimuli will be fixed (the standard stimulus; orange or turquoise) while the comparison stimulus will have its properties controlled by an adaptive staircase procedure. Participants will be instructed to report which of these two clearly visible (i.e., suprathreshold) stimuli is 1) brighter or 2) redder (for orange standard) or bluer (for turquoise standard). Manipulating the contrast of the comparison patch relative to the standard patch (which remains the same) allows for a precise measurement of a Just Noticeable Difference (JND) – the difference in luminance or chromatic contrast needed to make the two stimuli reliably different in appearance. The standard patch will be set to an intermediate hue (orange or turquoise) and at a luminance level brighter than the background, to mimic the appearance of disks in Lanthony’s D-15d test in which bipolar disorder participants have been reported to exhibit performance deficits (
Fernandes *et al.*, 2017). Administration takes ~20 minutes, including instructions and practice.

4) Pupil responses to light stimuli will be captured using a pupilometer capable of melanopsin-selective stimulation (OculoWise, Switzerland). Participants will first undergo 10 minutes dark adaptation before completing a post-illumination pupil response protocol, which measures pupil size in response to narrowband irradiance-matched red and blue light pulses. Similar protocols will then be administered using light pulses that (using the method of silent substitution) selectively target the cone-mediated luminance mechanism, and melanopsin. The resulting pupil responses are expected to provide a robust measure of increased retinal light sensitivity in bipolar disorder participants (administration ~45 minutes, including instructions and practice).

Session 2 - Visual evoked potentials (VEPs; EEG laboratory)

Participants will be able to take part in the EEG session either in the same afternoon (if they performed Session 1 in the morning) or on a separate day, depending on their preference.

Upon arrival, the EEG equipment will be set up and the electrodes positioned on the participant’s scalp. A BioSemi ActiveTwo (BioSemi, Netherlands) 64-electrode system will be used. Hypoallergenic electroconductive gel will be used to establish contact between the scalp and the electrode. Gel ensures a stable signal over a relatively long period of time.

We will measure VEPs elicited by contrast modulated patterns defined along the three retino-geniculate mechanisms (achromatic and chromatic). More specifically, pattern-onset and steady-state VEPs will be measured at multiple levels of contrast for uniform unipolar Gabor patches defined by increments and decrements along the achromatic, reddish-greenish and bluish yellowish axes. The experimental protocol will last for 1 hour.

EEG set up and removal will take approximately 60 minutes. An additional half-hour will be added to testing time to allow for participants to wash their hair in the laboratory’s hair-washing facilities after the data collection has ended, in order to remove the electroconductive gel.

**3.4.4.4
Part C: Retinal imaging
**

Part C involves three study visits to image the microstructure of the retina and to investigate longitudinal retinal changes over an 18 month period. The schedule for Part C study visits is 0-, 9- and 18-month time-points. Each imaging session will last about up to 1.5 hours.

Imaging will be conducted at the Edinburgh Imaging facility in the Queen’s Medical Research Institute on the BioQuarter Little France campus. Retinal scanning is non-invasive and a completely safe method of obtaining pictures of the retina. Images are fast to acquire, and non-contact, non-invasive and require only simple chin-rest positioning. Pupil dilation is not required for any of the imaging.

A trained member of the research team will image both eyes of a participant using:

1. Fundus camera photograph: A fundus camera generates a 2D, high resolution image showing the optic disc, macula and blood vessels, and permits analysis of these anatomical features.2. Ultra-widefield scanning laser ophthalmoscopy: An ultra-widefield scanning laser ophthalmoscope (UWF-SLO) captures more of the retina in one go (
^~^80%) and facilitates the study features and changes in the periphery (e.g. prevalence of drusen, and vascular abnormalities and integrity), though at the sacrifice of a lower resolution for an increase in image field.3. Optical coherence tomography (OCT): OCT images the retinal nerve fibre layer (RNFL) and inner layers of the retina.4. OCT Angiography (OCT-A): OCT-A reveals the very small capillary level vessels in the retina which are not possible to image in any other way.5. Optical biometry: Optical biometry yields the eye’s axial length - i.e. the distance from front to the back - a vital measure used to account for differences in individuals’ eyes and an important metric for the evaluation of retinal biomarkers.6. Automated perimetry: Automated perimetry tests a participant’s visual field. The participant sits in front of the machine and presses a button when they see the presentation of a white light stimulus in various locations of their visual field. This will reveal any functional changes over time which can then be compared to any structural changes detect with the other imaging techniques.7. Autorefraction: Autorefraction measures a participant’s refractive error (i.e. how short- or long-sighted they are).

Modes 1–4 of retinal scanning provide different but highly informative images of the back of the eye. Anonymised image data will be analysed by the relevant members of the research team in the Centre for Clinical Brain Sciences at the University of Edinburgh. There is a small risk that incidental findings may be identified on the retinal images which may require further investigation. We anticipate the rate of significant or urgent findings to be <1%. Each participant will be told of this risk, as well as it being stated on the participant information sheet. Should we observe unusual signs in the images that might signs of eye problems, anonymised images will be reviewed by the ophthalmologist on our team for checking of incidental findings. If we were to observe any such findings then an appropriate member of the study team would discuss this with the participant and inform their GP so that appropriate further tests and treatments could be arranged as necessary.

### 3.5 Data collection/participation windows

Baseline, Part B and Part C study visits and data collection will take place throughout the year.

Part A participant appointments and data collection will take place between the months of September and April (inclusive). Restricting data collection to these months avoids days with extremely long photoperiods (summer months) where night-time is limited or absent.

In the event of an abandoned study visit where a participant is unable to complete all protocol tasks, they will be invited back to complete the appointment at a later date if deemed appropriate by the study team.

The first screening and study visits (December 2023–March 2024) served as a pilot phase to fine-tune the assessments and/or their delivery. Protocol amendments were introduced where necessary

### 3.6 Study population

**
*3.6.1 Sample size calculation*
**

This study will assess 180 participants:

*n*=60 with bipolar disorder and currently on lithium therapy
*n*=60 with bipolar disorder and not taking lithium
*n*=60 healthy controls with no history of mental illness and no first-degree family history of mental illness

The required sample size for this study is calculated from melatonin measures relevant to Part A. This sample size is sufficient for both Part B and Part C of the project (see below). Sex and gender differences were not taken into consideration in study design or sample size calculations because there is no conclusive evidence of sex or gender differences in the primary study outcome measures.

**3.6.1.1
Part A Sample Size Calculation
**

Our subjects of interest are BD patients versus controls, with the BD group sub-divided into two groups: one where BD subjects are on lithium therapy and another where BD subjects are not taking lithium. Based on previous reports of light-induced melatonin suppression in BD (
Hallam *et al.*, 2009) we expect a difference of approximately 40–50% (Cohen’s d effect size 0.5–0.6) between the BD lithium group and the BD non-lithium group. As such, for 80% power with an alpha of 5%, we will need 42 participants in each of the three groups. Allowing for incomplete data collection in up 30% of participants, this means that we will recruit 60 participants in each group.

**3.6.1.2
Part B Sample Size Calculation
**

With this sample size (N=180 participants across three groups), a two-sided between-subjects t-test at 80% power with an alpha level of 0.05 will be able to reliably detect an effect size of d=>0.52, equivalent to a difference of 0.52 of a standard deviation (i.e., medium effect size). Comparably, a between-subject ANOVA with three groups would be able to detect an effect size of f=>0.23. For a clinical study of this kind, this represents a very high level of sensitivity. As a minimum, it will allow us to provide a more definitive characterisation of the observed phenomena than previous studies in this field. As a comparison, studies with groups of 20 participants, which are common in the existing literature, are capable of detecting an effect of d=>0.9 (two groups) or f=>0.41 (three groups), which are large effect sizes.

**3.6.1.3
Part C Sample Size Calculation
**

Part C is an exploratory study and is configured as the first step into investigating what sort of longitudinal retinal changes can be expected in a BD population. It is therefore difficult to estimate measurable effect size and very hard to predict which features will be discovered as relevant by computational approaches. However, the results of our analysis will be vital to informing future work. The samples size for Part C are thus informed by those of Part A and B, and an
*n*=60 per group is used as an achievable target for imaging a sufficient number of participants for developing, testing and assessing our methods.

**
*3.6.2 Inclusion criteria*
**

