### 2.2 Circadian rhythms are entrained to light

Circadian rhythms are endogenous near-24-hour rhythms which are continuously synchronised with the external light-dark cycle. The mechanism of this photic entrainment begins with photon absorption by intrinsically photosensitive retinal ganglion cells (ipRGCs) in the retina. This signals the presence of light to the hypothalamic suprachiasmatic nucleus (SCN), the core regulator of circadian rhythms. There are two main effects of photic signalling from the retina to the SCN. Firstly, light exposure acutely (and reversibly) suppresses the primary circadian-regulatory hormone, melatonin. Melatonin receptors are found throughout the central and peripheral nervous systems; thus, circulating melatonin levels signal external timings to the body. Secondly, light exposure at specific time windows has the ability to entrain the SCN clock by adjusting its phase. Given that the average free-running human circadian period is slightly above 24 hours, light in the morning is critical for maintaining circadian synchrony, whereas artificial light in the evening has the potential to significantly disrupt (or delay) it. A hypo- or hyper-sensitive response to light within the photoreceptive pathway can therefore result in a shifted circadian phase and dysregulation of biological rhythms.

There are a range of sensitivities to light within the general population, reflecting the varying influences of age, sex, pupillomotor function, and environmental light exposure upon photic response (
Chellappa, 2020;
Swope *et al.*, 2023). However, light sensitivity has been shown to be enriched in particular populations, causing conditions such as delayed phase sleep wake disorder (DPSWD) (
Watson *et al.*, 2018) which are characterized by considerable circadian dysregulation. Light sensitivity has also been identified as a feature of several mood disorders (
Swope *et al.*, 2023) and thus represents an opportunity for improving understanding, treatment, and potentially prevention of these conditions.

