**All participants**

Study participants must be adults ≥ 18 years old with capacity to give informed consent and to comply with the study design. All participants must be living in Scotland, be registered with a GP within NHS Scotland, and must have fluency in written or spoken English.

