### 3.10 Outcome measures

**
*3.10.1 Primary outcome measures*
**

**3.10.1.1
Part A
**

Difference in absolute change in plasma melatonin levels in response to light stimulation protocol between the 3 study groups.

**3.10.1.2
Part B
**

Difference in pupillometry, visual evoked potential, and chromatic discrimination/detection measures between the 3 study groups.

**3.10.1.3
Part C
**

Retinal structure differences between the 3 groups assessed over time

**
*3.10.2 Secondary outcome measures*
**

**3.10.2.1
Part A
**

To determine absolute differences in the following measures between the 3 study groups:

ALDA scale (Bipolar Disorder groups only)PSQI total score for sleep qualityMCTQ total score for chronotypeMEQ total score for chronotypeWHODAS 2.0 total score for global functionm-SPAQ total score for seasonal sensitivity

**3.10.2.2
Part B
**

Correlation of primary outcome measures with other, non-retinal measures acquired in the study (e.g. questionnaires, medical history), as well as with each other.

**3.10.2.3
Part C
**

Secondary outcomes include cross-sectional and longitudinal differences in retinal vascular metrics; retinal layer thickness; small vessel metrics; eye biometrics; visual field metrics. These outcomes will be correlated with other, non-retinal measures acquired in the study.

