### 3.11 Statistical analysis

**
*3.11.1 Proposed analyses*
**

**3.11.1.1
Part A analyses
**

We will compute the area under the curve for the melatonin profile using the trapezoidal method and also compute the percentage difference between the healthy control group and the BD lithium therapy group, as well as between the healthy control group and the BD non-lithium treatment group. We will then use one-way ANOVA (or Kruskal-Wallis) with post-hoc analyses (Tukey) across the three groups, as well as undertaking general linear model analyses controlling for potential confounding variables such as age, sex, ethnicity, educational attainment, employment status, socioeconomic status, smoking status, alcohol use, sleep quality, chronotype, psychiatric history, medication use and score on the Alda lithium response scale. 

**3.11.1.2
Part B analyses
**

Statistical analyses for the various measures (pupillary response, colour perception, spatiochromatic processing, visual evoked potentials) across the three groups will be performed using linear mixed effect models with healthy control group set as the baseline (i.e., zero) level for all the comparisons. Models will also be evaluated for the contribution of confounding factors, including age, sex, ethnicity, educational attainment, employment status, socioeconomic status, smoking status, alcohol use, sleep quality, chronotype, psychiatric history and medication use and score on the Alda lithium response scale.

**3.11.1.3
Part C analyses
**

We will test the hypothesis that people with BD have significant differences in structural and functional measures of the retina and in the trajectory of change compared to controls. Additionally, we will assess whether individuals with BD who are taking lithium have an attenuated trajectory of change compared to those with BD on other medications. Student’s t-test and generalised estimation equations will be used to examine differences in retinal measures and psychophysical thresholds between the three participant groups. Spearman’s rank correlation coefficient will be used to investigate associations of retinal measures and psychophysical thresholds with other key parameters from the study data, including confounding demographic and clinical factors. Trajectory analysis will be used to assess changes in retinal parameters and psychophysical thresholds over time and how effective this approach is at stratifying participants.

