### 3.16 Ethical considerations of the research

1. Ensuring inclusive and representative recruitment:

Our recruitment methods are based on voluntary contact from interested individuals who have been informed of the study either through established research and mental health organisations, or via social media. However, it is known that particular identities are under-represented in medical research, with serious consequences for equitable healthcare. In particular, people from minoritised ethnic groups, people at socioeconomic disadvantage and people with minoritised sexualities and gender identities are under-represented and under-served by research. The reasons for this are many and varied. In this study, we aim to achieve a representative and diverse study population, with equal representation of men and women. We will advertise the study widely, and we will recruit thoughtfully to ensure our sample is representative of the bipolar disorder population in Scotland. We will also provide reimbursement for caring costs (e.g. childcare) to remove barriers to participation for those with caring responsibilities.

2. Preventing undue incentivisation due to participation payments:

Study participants will be reimbursed for their time and travel expenses. However, it is important that financial benefits do not inappropriately incentivise individuals to participate in the research when it is not in their best interests. The participation payment will therefore be advertised in a neutral tone in any study advert materials and in the Participant Information Form. We recognise that offering payment for study participation may increase the possibility of dishonesty from people who want to participate in the research, in order to increase their chances of enrolment. We will address this by using NHS-linked recruitment methods and by corroborating information with medical notes where necessary.

3. Risks and adverse events associated with study procedures:

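### Section 3.6.1 leaves sex out of the design for lack of evidence, yet the article elsewhere treats age and sex as influences on photic response and as confounders, and no adjusted Part A contrast is made decisive

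*Protocol article*

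**What the plan says.** Section 3.6.1 states: "Sex and gender differences were not taken into consideration in study design or sample size calculations because there is no conclusive evidence". The reason in full is that there is "no conclusive evidence of sex or gender differences in the primary study outcome measures". The sentence does not mention age.

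Section 2.2 explains the spread of light sensitivity in the general population as "reflecting the varying influences of age, sex, pupillomotor function, and environmental light exposure upon photic response".

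The Part A primary outcome (3.10.1.1) is "Difference in absolute change in plasma melatonin levels in response to light stimulation protocol between the 3 study groups". Part B's primary outcomes include pupillometry. Both are responses to light.

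For Part A, section 3.11.1.1 states: "We will then use one-way ANOVA (or Kruskal-Wallis) with post-hoc analyses (Tukey) across the three groups". Alongside this it plans "general linear model analyses controlling for potential confounding variables such as age, sex, ethnicity" and a longer list that ends with psychiatric history, medication use and the Alda score. For Part B, section 3.11.1.2 evaluates mixed models for the same factors.

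On who enters the groups, the age criterion in section 3.6.2 is "Study participants must be adults ≥ 18 years old", with no upper limit given. Section 3.16 aims for a study population "with equal representation of men and women". That aim concerns the sample as a whole, not balance between the three groups.

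**The concern.** This is a non-randomised comparison. Membership of the lithium, non-lithium and control groups follows from diagnosis and existing treatment, so nothing in the allocation equalises age or sex. If those factors affect the melatonin response, as section 2.2 suggests for photic response generally, a difference in age or sex mix can look like light hypersensitivity or its attenuation by lithium. It can equally hide either one.

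The stated reason for setting sex aside sits badly with the rest of the article, which treats sex as an influence in the background and as a confounder in the analysis. The practical question is which Part A result answers the study question: the unadjusted comparison, or an adjusted one whose covariate list does not suit a three-group contrast.

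**Working it through.** **The plan's own figure.** For 80% power at two-sided 5%, n per group = 2(1.960 + 0.842)² / d². At d = 0.6 this is 2 × 7.85 / 0.36 = 43.6, so 44 (45 by the t-test), within two or three of the stated 42. Allowing for 30% incomplete data, 42 / 0.7 = 60. So 42 (analysed) and 60 (recruited) per group bracket the calculations below.

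**Setting the sections side by side.** Section 2.2 says that sex influences photic response. Section 3.6.1 says that evidence for the primary outcomes is not conclusive and draws a design decision from that. Section 3.11 then names sex as a potential confounder in Parts A and B. The three statements need an explanation that the article does not give.

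**The covariate list.** Section 3.10.2.1 restricts the Alda scale to the bipolar groups, so it has no value for controls. Section 3.6.3 excludes from the control group recent psychiatric illness, recent psychotropic use and past severe mental illness, while lithium use separates the two bipolar groups. Psychiatric history and medication use therefore largely restate group membership. A model holding all of these cannot estimate a clean three-group contrast. A model holding age and sex can.

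**Possible size.** The documents give no age gap, age correlation, sex effect or sex mix by group, so everything here is assumed.

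- Age: shift = (r / SD of age) × gap. With r = 0.3, SD 14 years and gap 8 years, 0.3 / 14 × 8 = 0.171 SD.
- Sex: shift = sex effect in SD × difference in the share of women. Examples: 0.2 × 0.10 = 0.02; 0.3 × 0.20 = 0.06; 0.5 × 0.30 = 0.15.
- Noncentrality = shift / √(2/n). For 0.171 this is 0.786 (n = 42) and 0.939 (n = 60).
- The Tukey critical value on the t scale is q(0.95; 3 groups, 3(n−1) df) / √2: 3.355/√2 = 2.372 (n = 42) and 3.343/√2 = 2.364 (n = 60).

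Probability of declaring a given pair different when there is no true difference (noncentral t), at 42 / 60 per group:

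| Assumption | Shift (SD) | Uncorrected two-group test | Tukey pair |
|---|---|---|---|
| No imbalance | 0 | 5.0% / 5.0% | 1.9% / 1.9% |
| Sex effect 0.2, 10 points | 0.02 | 5.1% / 5.1% | 2.0% / 2.0% |
| Sex effect 0.3, 20 points | 0.06 | 5.9% / 6.2% | 2.4% / 2.6% |
| Sex effect 0.5, 30 points | 0.15 | 10.4% / 12.9% | 5.0% / 6.4% |
| Age gap 8 years | 0.171 | 12.1% / 15.4% | 6.0% / 8.0% |

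The normal approximation gives 10.6% and 13.0% for the largest sex case. With r from 0.2 to 0.4 and a gap of 5 to 10 years, the shift runs from 0.07 to 0.29 SD. The Tukey figure then runs from 2.6% to 21.5%, and the uncorrected figure from 6% to 34%.

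The overall ANOVA F-test, with one group shifted by 0.171 SD, rejects in 11.5% / 14.7%. With the third group halfway between the other two it rejects in 9.8% / 12.1%.

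**How much sex imbalance is plausible.** If half of each group are women on average, chance alone gives a 95% range of ±1.96√(0.5/n) for the difference in shares: about ±21 points at 42 and ±18 points at 60. Systematic differences would come on top.

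**Masking.** If the true effect is d = 0.5 and a 0.171 SD shift runs against it, the power of the uncorrected two-group comparison falls from 62% to 32% (n = 42) or from 78% to 43% (n = 60).

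**The case against.** The strongest reply has four parts.

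- **The statements can be reconciled.** Section 2.2 is background on the general population; section 3.6.1 makes a narrower claim about conclusive evidence in these outcomes. Both could be true. This stands in so far as the conflict is not a strict logical contradiction. But light-induced melatonin change and pupil response are photic responses, and section 3.11 treats sex as a confounder, so the sentence still needs an explanation.
- **Adjustment is already planned.** This stands and removes much of the consequence: a correctly specified model with age and sex takes out the bias shown above. A reader might infer that the unadjusted ANOVA is the primary analysis because it is named first. Section 3.11.1.1 does not say so; it ranks neither analysis.
- **The choice of deciding model belongs in the analysis plan.** This stands in part; the bare absence of a ranking would be no finding. The listed covariates, however, are in the article, and as listed they do not suit the three-group question.
- **The illustrated size can be overstated.** A reader might take 12–15% as the false-positive rate. That comes from an uncorrected two-group test with assumed age inputs. The planned Tukey comparison gives about 6–8% per pair, although the overall F-test does reach 10–15% on the same inputs.

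Three further readings go beyond the text. One is that age was deliberately left out of the design: section 3.6.1 speaks only of sex and gender. Another is that the groups are known to be unmatched: a condensed article may omit balancing that the full protocol contains. The third is that every primary outcome is affected: section 2.2 concerns photic response and does not reach the retinal structure measured in Part C.

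**Conclusion.** The point holds in a limited form. The reason given in section 3.6.1 does not fit sections 2.2 and 3.11, and the unadjusted Part A comparison is open to confounding by age and sex in groups that were not randomised. The exposure concerns Part A melatonin and, through section 2.2, Part B pupillometry, where confounder-adjusted models are already foreseen.

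The size cannot be determined from the documents. Under the assumed 8-year gap, age SD of 14 and correlation of 0.3, the excess is about 4 to 6 percentage points per Tukey pair (6.0% or 8.0% against 1.9%). For modest sex imbalance it is at most about 1 percentage point, whether the test is corrected or not. This is a matter of wording and specification that should be settled before analysis. It does not show the design to be unsound.

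**What to change.** 1. In section 3.6.1, rewrite the sentence so that it agrees with sections 2.2 and 3.11. It can say that sex was not used in sizing the study, that age and sex may influence photic response, and that both are handled by adjustment. If the full protocol balances the groups on either factor, say so.
2. In section 3.11.1.1, name the three-group contrast adjusted for age and sex as the deciding Part A result and label the one-way ANOVA with Tukey as descriptive. Keep the Alda score, medication use and psychiatric history out of that model, and use them only in analyses within the bipolar groups or in sensitivity analyses.
3. Optionally, monitor the age and sex mix by group during the remaining recruitment. Matching controls and non-lithium participants to the lithium group should not be required, because it could work against the representativeness that section 3.16 aims for.

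The cost is a change of wording. Age and sex are already collected. A linear age term and a sex term use two degrees of freedom out of 123 (3 × 41) with 42 per group. No extra participants or visits are needed.
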